# Project summary

A remarkably effective initiative to improve health worker performance was developed by a District Health Officer in a hill district (Doti) of Nepal in 2009. This study will generate further understanding of this model and replicate an improved version of the model it in different ‘intervention’ contexts (mountain, hill, and plains districts). A multi-method process evaluation will be used to document the development and implementation processes involved, assess effectiveness and scale-up feasibility.

*Aim:* To assess the processes and effectiveness of a health workforce performance model (HWPM) in improving staff performance and health outcomes and its scalability in Nepal

*Objectives:*

1. To identify lessons from Doti District pilot intervention on improving effectiveness and efficiency of health workers and develop an understanding of what worked, how and why;
2. To analyse the context in the 3 intervention districts (mountain, hill and plains) and ascertain implementation issues and strategies
3. To develop, refine and test a HWPM model in 3 different districts, assess processes, effectiveness and scalability

*Intervention:* The key components of the HWPM in Doti included: group monitoring and assessment; individual appraisal; supportive supervision and feedback; development of outcome focused job aid of health workers, and community assessment. We will conduct a process evaluation of the HWPM experience in Doti, followed by a contextual analysis of intervention districts (3). An interactive workshop with policy makers, district staff, community and health professional organisations, informed by the process evaluation of the pilot, contextual analysis in the 3 intervention districts and a review of international experience of similar initiatives, will be used to develop a contextually feasible HWPM. Following orientation of district managers the improved HWPM will be implemented in the 3 intervention districts.

*Methods:* This is an implementation research, using a mixed method process evaluation. Qualitative approaches will include in-depth interviews, focus group discussion, ethnographic observations, and participatory observation techniques. These techniques, together with an analysis of relevant routine health service data, will generate an in-depth understanding of the context, implementation processes and changes in context during implementation in districts and at national level. Analysis of data through time, including base-line and endline data collection will support further understanding of implementation issues. Changes in staff motivation will be measured before and after the intervention using a tool which will be adapted to the Nepal context following the Doti process evaluation for assessing health worker motivation and satisfaction drawing on existing validated tools.^1,2^ Baseline quantitative data on health service delivery outcome indicators will be collected using record review of district-level facility data; implementation evaluation (inputs and outputs) and their relevance with respect to attaining desired outputs; in-depth understanding of changes in outputs (what worked or otherwise and why and how); and detailed documentation of overall factors that facilitated and hindered the intervention, and plausibility of scalability of the intervention will be documented.

*Study site:* Purposive selection of 3 districts, one from each ecological zone (mountain, hill and plains).

*Expected Outcomes:*

*Understanding what works where, why and how:* A tested and improved HWPM, documented understanding of the processes involved in the HWPM in Doti and the 3 different implementation districts; a HWPM implementation guide and training manuals

*Anticipated effectiveness outcomes:* increased motivation of health care workforce delivering quality health care services, increased functionality of health facility and reduction in staff absenteeism*;* Improved health service delivery outcomes (i.e. maternal and child health)

*Tentative time frame:* 24 months in total: process evaluation of the pilot and contextual analysis of implementing district 1-6 month; develop materials and tools for intervention package 7-8 month; intervention and process evaluation 9-20 month; final evaluation and write-up 21-24 month.

# Detailed description of the project

**Background information and rationale**

A well-performing workforce is described by WHO as one in which staff are available, competent, responsive and productive.^3^ Several studies have identified limitations within Nepal’s health workforce in all of these aspects. For example, health facility surveys have shown that only 64-80% of doctors, 68-81% of nurses and 81-92% of paramedics are available for work.^4^ These Human Resource (HR) problems have a direct impact on health service delivery, particularly maternal and new born services, e.g. the lack of staff to support safe delivery in government facilities was not due to the lack of trained staff but the inability to attract and retain them.^5^ The impact of supervision has also been assessed in a sample of districts and only found to have a minimal impact on health service delivery,^6^ hence lack of supportive supervision continues to be an issue. Recent capacity assessments of the health sector workforce have identified the need to strengthen leadership and management.^7^ Studies have found that HR issues – recruitment, deployment, retention and motivation – are very much context specific and vary within mountain, hill and Terai (plains) districts. A further limitation in the development of leaders is highlighted by the observation of the “drifting away of senior female staff across the health sector”.^8^ The lack of opportunities for career progression affects women across Nepal’s health sector and serves to de-motivate female staff.

Practical experience aligns with these studies, the Director of National Health Training Centre (collaborator on this study) who developed the pilot in Doti, and other DPHOs have identified the following issues from workforce assessments and from the direct experience:

- High turn-over and poor retention of staff.
- Lack of job descriptions, and when they do exist, they tend to be based on tasks rather than overall outcomes.
- Limited supervision, particularly supportive supervision that is effective in improving health workforce performance hence health outcomes.
- Lack of context specific action planning to resolve HR performance problems when identified
- Lack of accountability to communities.

Much of the evidence of what works in improving workforce performance is based on the understanding of the complexities of the factors influencing staff.^9,10^ These complexities require integrated HR strategies, described by Buchan as “linked and coordinated HRM interventions [that are] more likely to achieve sustained improvements in organisational performance than single or uncoordinated interventions”.^11^ WHO recommends considering HRM in conjunction with other key elements of the health system, particularly health information, health financing, leadership and governance, and access to essential medical products, vaccines and technologies and health services.^9^

Output 3 of the recent Human Resource for Health (HRH) Strategic Plan focuses on the improved performance of health workers and emphasises the need to strengthen performance related supervision, particularly through the development of job descriptions and review processes. The HRH Strategy provides a valuable and timely opportunity for testing the proposed intervention as MoHP is looking for evidence of the effectiveness of interventions that can be scaled up.

The intervention in this study was developed by a District Public Health Officer (DPHO) (now Director of NTHC as above), based on international HRM evidence, but applied and simplified to fit the health system context in Nepal. The intervention consisted of: group monitoring of health facility and feedback; supportive team and individual supervision, outcome focused revised job aid, peer evaluation and mentoring. Initially developed in Doti District (Far West), the HR strategies tried appeared to have had a positive impact on maternal mortality, with increases in births attended by an Skilled Birth Attendant (SBA) (from 11.44% in 2009/10 to 22.7% in 2010/11 DoHS) and in the proportion of women having 4 Antenatal Care (ANC) visits (29.77% in 09/10 and 43.95% in 10/11). The extent to which this intervention is appropriate to other districts in Nepal and the processes and costs involved are not yet known. With the publication of the HRH Strategy 2012, testing an intervention that shows promise in improving health workforce performance and thus health outcomes, is both timely and necessary. We will adapt the intervention to fit the realities of 3 different districts in Nepal and document processes, costs and its scalability.

##

## Study goal and objectives

Goal: A health care workforce performing effectively and efficiently to deliver quality health services

Aim: To assess the processes and effectiveness of a health workforce performance model (HWPM) in improving staff performance and health outcomes and its scalability in Nepal

*Objectives:*

1. To identify lessons from Doti District pilot intervention on improving effectiveness and efficiency of health workers and develop an understanding of what worked, how and why;
2. To analyse the context in the 3 intervention districts (mountain, hill and plains) and ascertain implementation issues and strategies; and
3. To develop, refine and test a HWPM model in 3 different districts, assess processes, effectiveness and scalability

*Innovation being tested:*

The innovation was developed by District Public Health Office (DPHO) in Doti district where it proved to be successful in increasing health outcomes. Adapting and extending the approach to 3 more districts will allow it to be tested in different contexts and gain an in-depth understanding of feasibility to scalability.

The key components of the intervention are as follows:

Table 3: Key components of the intervention

| **Strategy** | **What does it involve** | **Purpose** |
| --- | --- | --- |
| **1. Institutional Level: Group Monitoring and action planning** | Initially bi-annually and subsequently annually, a team of peers visit health facilities and grade them against routine indicators, particularly those on maternal and child health and aspects of health worker performance such as absenteeism, regularity of appraisals and training undertaken. The facility appraisal is conducted in the morning and in the afternoon an action-planning workshop is held for facility staff to identify practical solutions that they can do to improve any of the issues identified in the monitoring visit. (DPHO, HFMC, FCHVs and other HF staff) | To recognise good practice and motivate those on the monitoring group to learn and try similar approaches in their own facilities.  To identify poor practice and pragmatic ways of addressing these.  To establish a sense of supportive competition between health facilities. |
| **2. Community Assessment** | Community assessment of facilities and action planning are an integral part of the group monitoring exercise. During the peer monitoring visit, officers from DPHO and members of the HFMCs conduct rapid participatory appraisal PRA exercises with communities to identify the positive aspects of the health facilities and the areas they wish to improve. This community feedback is then presented along with the group monitoring feedback to the facilities’ action planning workshop.  During the workshop the facility staff and the HFMCs are facilitated by the group monitoring team to identify specific actions they can undertake to improve their health facility. The emphasis is on the actions being achievable by the clinic staff themselves, rather than requiring external financial or other assistance. | To improve accountability and ensure staff feel motivated to provide a service that meets the needs of their communities.  If positive feedback is received this can motivate staff.  If negative feedback is received this can encourage staff to make changes so as not to appear to be letting their communities down. |
| **3. Supportive supervision and feedback** | Health workers are appraised regularly (at least annually) by their colleagues. Each HW is appraised by four other staff: 1 from the DPHO, 1 colleague of the same professional level from outside the health facility and from the same level HF and 2 colleagues from within the health facility (normally one will be the in-charge). Individual workplans in line with the targets for the health facility will be set. While this intervention goes against the hierarchical relationships found within Nepal’s health workforce, it has been seen to work within Doti district particularly with a strong lead from the DPHO, who clearly endorsed the approach. | To reduce bias which may occur when appraisals are done by only one manager, normally the in-charge.  To encourage professional development through peer support  To link performance review with action plans to improve performance in line with facility targets. |
| **4. Outcome focused Job Descriptions:** | Managers at District and Facility level are trained to review job descriptions and to rewrite these in a participatory way with their staff to address targets for their health facilities.  Staff are facilitated by managers to write their own job descriptions. These job descriptions are to focus on the targets and outcomes to be achieved rather than the tasks to be completed. | To ensure all health workers are clear on their roles and responsibilities  To build a sense of purpose among health workers  To build the leadership and management skills of in-charges (facility line managers) and district managers. |

The diagram below illustrates how the inputs, outputs and outcomes aim to not only improve workforce motivation and performance, but also how the close engagement with policy makers in National, Regional and District level will inform the development of HR systems across Nepal. This proposal comes at a time of great opportunity for policy change and influencing practice, due to the recent approval of an HR strategic plan and the development of the 3rd Nepal Health Sector Programme (NHSP). This process is illustrated below:

**Figure 1: Impact of the Study at District and National Level**

**Context:** low motivation of health workforce, non-availability of staff, absenteeism, lack of supportive supervision and feedback, poor performance appraisal system, high turnover and retention of health workers, unclear job aid and unfocused, lack of accountability to community

**OUTPUTS**

- Process evaluation report from the pilot district with documented lessons of what worked, how and why
- Context analysis report of 3 intervention districts (baseline information - qualitative and quantitative) with a detailed analysis of the context in mountain, hill and plain districts and understand implementation issues and strategies
- Final intervention model and implementation guide
- Trained and skilled district managers and supervisors, health workers and health facility management committee members to implement the model
- Proper documentation of operational feasibility and constraints of the model (what worked or not, why and how)
- Greater understanding of scalability of the model - feasibility, cost (additional)
- Ownership and acceptability fostered in implementing districts

**OUTCOMES**

**NATIONAL LEVEL:**

- A tested and improved costed HWPM supported by an implementation guide and training manuals with documented understanding of processes involved

**DISTRICT LEVEL**

- Motivated and higher performing health workers and increased health facility functionality
- Improved health service delivery outcome indicators in implementing districts, e.g. ANC, institutional delivery, TB case finding, Childhood immunisation

**INPUTS**

- Process evaluation of the pilot district
- Context analysis of implementation districts (3- Mountain, Hill and Terai)
- Adapt and refine Health Worker Performance Model in an interactive workshop (informed by pilot and district context analysis)
- Train District Manager, District Supervisors, Health Workers and members of Health Facility Management Committee on HWPM
- Implement intervention (group monitoring, supportive supervision and feedback, improved performance appraisal system),
- Monitoring and evaluation - an ongoing process
- Methods used: Qualitative approaches (in-depth interviews, focus group discussion, ethnographic observations, and participatory observation techniques); and Quantitative approaches (baseline and endline data on health service delivery indicators using record review of district-level facility data, analysis of data through time, staff motivation will be measured before, during and after the intervention using a tool for assessing health worker motivation and satisfaction)

**Aim:** To assess the processes and effectiveness of a health workforce performance model (HWPM) in improving staff performance and health outcomes and its scalability in Nepal

## Expected outcomes

The overall outcome of this study will be a clear understanding of the most appropriate way to implement the health worker performance model (HWPM). In particular, the study will identify what works in different geographical, cultural, governance and health facility contexts, why and how the model works in these contexts. The strong links of the study team with national policy makers means that we also expect this understanding of how the model works to influence the HR policy and practice across Nepal. In the most effective decision making environments, all relevant parties – researchers, decision-makers and other stakeholders, including civil society actors, work together as interdependent allies in an environment of mutual trust and respect. This enables major decisions to be based on a solid foundation of evidence and benefit from a broad range of inputs. Throughout this study we intend to work with decision-makers to create this positive environment for change in HR systems in Nepal’s health sector.

The output of the study will be a detailed, documented understanding of the processes involved in the HWPM in Doti and then in the implementation of the model in three districts from different geographical and cultural regions, with different levels of performance and functionality of governance systems and in all levels of health facility. This detailed understanding will increase the knowledge available to policy makers and practitioners wishing to implement the HWPM in different context. To aid them to do this a HWPM implementation guide and training manual will be produced.

In order to develop this detailed understanding we propose conducting detailed case studies, at least 4 in each of the 3 districts, of the process of implementation of the HWPM over a 20 month period. These case studies will each be centred on a health facility, and in each district a health facility of each level (Hospital, PHCC, Health Post and Sub Health Post) will be included. This will give a detailed understanding of implementation issues at different levels of the health system and for different cadres of staff. The purposive sampling will ensure that perspectives from male and female staff of different castes and ethnicities captures any variations in how the HWPM can best work with all staff.

*Anticipated effectiveness outcomes:* increased motivation of health care workforce delivering quality health care services, Increased functionality of health facility and reduction in staff absenteeism*;* Improved health service delivery outcomes (i.e. maternal and child health)

In-depth documented context specific (district) *understanding* of the processes involved in the intervention from the perspectives of different stakeholders

*Anticipated effectiveness outcomes:*

- **Increased motivation of health care workforce delivering quality health care services:** motivation of health workforce will be measured before and after the intervention using a tool for assessing health worker satisfaction. Two tools will be piloted in Doti and an adapted tool appropriate for the Nepal context will be used to measure motivation before and after the intervention in three districts. ^1,2^

Staff motivation is seen here as a process outcome that ultimately influences health service utilisation outcomes, particularly maternal and child health. The two years of this study intervention may not be sufficient to see impacts on health outcomes, however these will still be collected as secondary outcomes in order to explore possible relationships. The qualitative data will also help to elucidate these linkages and motivation level at different stages of intervention.

- **Increased functionality of health facility and reduction in staff absenteeism:** functionality related outcome to be measured using facility records: service utilisation register (OPD), and staff attendance register. The proportion of official open days for which the clinic is open and the provider is in place before and after the intervention will be measured. Qualitative interviews with community people (including households nearby health facility), service users, and members of health facility management committee will be conducted to validate facility records.
- **Improved health service delivery outcomes:** all health service delivery outcomes measure proposed are based on data that is routinely available through the HMIS system. Measures will be assessed before the intervention is implemented and one year later. Qualitative interviews will be conducted to further understand what drives the success or otherwise of the intervention. The following health service delivery indicators will be measured: the proportion of deliveries conducted by a skilled birth attendant at home and in a government health facility (denominator is expected pregnancies DOHS); the proportion of women who have 4 ANC checkups (denominator is expected pregnancies DOHS); Childhood immunisations: the proportion of children who receive DPT1 who also receive DPT3 within 4 months after birth before and after the intervention.

**Dissemination/scalability:** These outcomes are strategic in supporting scalability, the primary outcomes provide a tested model with supportive documents to guide scale up and in depth understanding of the processes within. Monitoring the secondary outcomes will help further develop the evidence base. Dissemination of the study will be done in presence of officials of Department of Health Services and the Ministry.

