### **Analysis**

*Motivation Tool:* All quantitative data will be double entered into CsPRO. Checks will be run to identify missing data and any anomalies. Data will be exported to STATA to carry out the quantitative analysis. The characteristics of health workers and their places of work will be presented for each district to identify any significant differences that may lead to bias. The difference in mean scores from the motivation of HW tool before the intervention and after will be analysed using ANOVA to identify any significant differences (shown with 95% CIs and p values). Regression analysis will be used to identify the influence of various variables on the main outcome of staff motivation. For example, difference due to gender, age, level of health worker, place of work (hospital, PHCC, HP, SHP). Factors such as other HR initiatives or health systems changes will also be recorded and included in the analysis as they potentially be confounders.

*Routine Health Service Data:* Frequency tables with proportions will be used to compare secondary outcomes across districts. Where possible trend data from health sector annual reports over the last 5 years will be used to avoid over interpretation of data peaks.

*Qualitative data:* Ritchie and Spencer’s ‘framework’ approach will be used to analyse the qualitative data.^12^ The advantage of this structured approach is that the thematic framework can be closely based on the research objectives but also allows for other themes to emerge from the data. The transparent structured approach supports collaborative analysis. There are 5 key stages within framework approach:

1. Familiarisation: Here the analyst reads through transcripts and notes pulling out key ideas and starting to identify recurrent themes. This process will be done by two HERD researchers independently.
2. Identifying a thematic framework: In this step of the process a framework is constructed based on issues from the original research aims, emergent issues from the participants and the recurrent themes identified during the familiarisation process. At this point the cross-cutting themes of motivation, gender, management styles, other health system issues within the framework to see how perceptions and issues differ across these groups. The 2 LSTM ([name]) consultants will work with HERD researchers to develop the framework.
3. Indexing: Here the thematic framework is applied to the data.

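### The DPT indicator puts a 4-month-from-birth limit on DPT3 but no age or cohort limit on DPT1, so one figure mixes retention with age at first dose

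*Protocol*

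**What the plan says.** The definition is in the protocol, Expected outcomes, under improved health service delivery outcomes: "the proportion of children who receive DPT1 who also receive DPT3 within 4 months after birth before and after the intervention". The same paragraph states that "all health service delivery outcomes measure proposed are based on data that is routinely available through the HMIS system" and that "Measures will be assessed before the intervention is implemented and one year later".

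No other section adds an age or cohort limit for DPT1. The district-level outcomes only name the topic: "Improved health service delivery outcome indicators in implementing districts, e.g. ANC, institutional delivery, TB case finding, Childhood immunisation". The end-line list of routine indicators in Step 4 does not mention immunisation.

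The status of the outcome is modest. Of the health outcomes the protocol says that "these will still be collected as secondary outcomes in order to explore possible relationships", and it warns that the study period may be too short to show an effect on them. The planned analysis is descriptive: "Frequency tables with proportions will be used to compare secondary outcomes across districts".

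**The concern.** Numerator and denominator follow different clocks. Entry to the denominator depends on receiving a first dose, at an age the protocol does not restrict. Entry to the numerator depends on age at the third dose. A child whose DPT1 comes after 4 months is counted below the line and can never be counted above it. A child who starts somewhat earlier, but too late to fit the remaining doses in, is in the same position.

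The figure can therefore move for two unrelated reasons: more children who start go on to finish, or children start at a different age. Bringing in children who would otherwise have had no vaccine pulls the figure down when they come late. That matters because the intervention aims to keep facilities open and staffed on more days, which could plausibly change who starts and when. It also matters for the planned comparison across districts, which were chosen to differ in geography and culture. A difference in age at first dose between them would appear in this indicator even if nothing changed over time.

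**Working it through.** The protocol states no rate, sample size or power for this indicator, so there is no figure of its own to reproduce. The check takes the definition literally and asks how it behaves.

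**Latest first dose that can still count.** Four months is 4 × 365.25 / 12 / 7 = 17.4 weeks. The protocol gives no dose interval, so this is an assumption shown as a range. With 4, 6 or 8 weeks between successive doses (8, 12 or 16 weeks from DPT1 to DPT3), the latest usable age at DPT1 is:
- 17.4 − 8 = 9.4 weeks
- 17.4 − 12 = 5.4 weeks
- 17.4 − 16 = 1.4 weeks

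A first dose after 17.4 weeks cannot count whatever the interval.

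**Form of the indicator.** Let c be the share of DPT1 recipients who receive DPT3 at any age, and L the share who start too late. Assume that c is the same for early and late starters, and that early starters who finish do so by 4 months. Then the indicator is c × (1 − L), and it cannot exceed 1 − L.

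| L | c = 0.80 | c = 0.90 |
|---|---|---|
| 0.10 | 0.72 | 0.81 |
| 0.20 | 0.64 | 0.72 |
| 0.30 | 0.56 | 0.63 |
| 0.40 | 0.48 | 0.54 |

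Both c and L are assumed; neither is in the documents.

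**Change over time.**
- L stable at 0.20, c rising from 0.80 to 0.90: the indicator goes from 0.64 to 0.72. The direction is right; the 10-point gain shrinks to 8, that is, 10 × (1 − 0.20).
- c stable at 0.90, L falling from 0.30 to 0.20: 0.63 to 0.72, a 9-point rise with no change in retention.
- c rising from 0.85 to 0.95, L rising from 0.20 to 0.30: 0.68 to 0.665, a slight fall although retention rose by 10 points.

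**Between districts.** Two districts with the same c = 0.90, but L = 0.10 and 0.30, would be tabulated as 81% and 63%.

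**Reaching late starters.** Take 100 children, of whom 80 start early and 72 of those finish by 4 months. If the other 20 never start, the indicator is 72/80 = 90%. If those 20 are instead reached late and all finish, it becomes 72/100 = 72%, while retention is (72 + 20)/100 = 92%. With all 100 children as the denominator, timely DPT3 is 72/100 = 72% in both cases. The fall from 90% to 72% comes only from the choice of denominator.

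**The case against.** The strongest reply is that the protocol never calls this a completion or drop-out measure. It writes an explicit timeliness condition. On that reading a child whose third dose comes after 4 months is rightly outside the numerator, and a rise because children start earlier is a real service gain. This stands. A reader might infer that late starters who finish are wrongly recorded as non-completers; the text does not support that, because it does not say that completion is what is being measured. The mismatch remains on the timeliness reading all the same. A timely-dose measure needs a denominator fixed by age or birth cohort, and with DPT1 recipients as the base, late outreach lowers the figure, as the 100-child example shows.

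A reader might also infer that the two components could never be separated afterwards. The documents do not support that either. Step 1.2 draws the baseline from facility registers as well as HMIS data, Step 3 collects both through time, and the data quality section verifies routine data at the sampled facilities. If the registers hold dose dates, some separation may be possible. The protocol does not plan it.

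Three further points stand. The absence of an age limit on DPT1 is read from silence, and an extraction plan could add one. The same definition applies in both rounds, so with a stable late-starter share the direction of change is preserved. And nothing in the documents shows that this share will shift.

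**Conclusion.** The concern holds as a defect in how a secondary outcome is defined. As written, the indicator mixes retention from DPT1 to DPT3 with age at first dose, and it falls when more late starters are reached. It fits neither a retention measure nor a timeliness measure cleanly.

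Its size cannot be established from the documents. The figures above rest on assumed dose intervals, retention and late-starter shares, on equal retention in early and late starters, and on early starters finishing inside the window. The before-after change is confounded only if the late-starter share shifts; a comparison between districts is affected whenever that share differs between them. The outcome is exploratory and descriptive, with no test or power claim, and the motivation score is untouched. The wording is worth correcting, but the main conclusions do not rest on it.

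**What to change.** Before baseline extraction, replace the single indicator with two lines, each defined identically in both rounds:

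- **Retention from DPT1 to DPT3**, without the age-from-birth limit, from routine DPT1 and DPT3 counts. If register dates allow, define it instead as DPT3 within a fixed interval after DPT1.
- **Timely DPT3**, by 4 months of age as the authors wrote it, with a denominator matched by age or birth cohort rather than all DPT1 recipients.

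This keeps the 4-month condition and makes clear which component has moved. The cost is one extra reported line, plus dose dates from the registers if the dated versions are used. The count-based retention line stays within routine data, but it compares totals rather than following the same children, and the report should say so. The change concerns only how the outcome is counted, not the vaccination schedule.
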